### Ethics

The protocol has been approved by the Ethical Board of the Balearic Islands, Spain (n° IB 733/06 PI).

## Discussion

If we assume that the prevalence of depression is increasing in western countries, it is necessary to search for reasons which might explain it [1]. One reason could be the lifestyle of the population, which we know is changing in recent decades. A significant proportion of the population has reduced their physical activity while following a less healthy diet [8,11]. In addition, there is a tendency to sleep fewer hours and be less exposed to sunlight [18,19]. We know that these changes in lifestyle have an impact on brain physiology that may increase depression vulnerability [7,12]. There are also very suggestive evolutionary explanations in this regard. As a species we have evolved under the selective pressure of vigorous physical activity, essential for success in the harvesting, hunting and scavenging that allowed our ancestors to survive. This activity took place outdoors and conditioned our diet and our way of living. It is therefore possible that changes in lifestyle of the population in the developed world are contributing to increase depression vulnerability. This study is based on this hypothesis.

Sleep control, exercise, diet and sunlight exposure have been separately recommended by several research groups as treatment for patients with Depression [28-30]. However, there is very little research on the usefulness of combining these simple hygienic-dietetic measures. There is an open study that successfully combines three recommendations (exposure to sunlight, exercise and vitamin pills) in a sample of women without antidepressant treatment [28]. Other studies associate light therapy and exercise programs in subjects with sub-threshold depressive symptoms [29]. Finally, another study uses sleep deprivation and light therapy in combination with psychopharmacology in bipolar patients suffering depressive symptoms [30]. All of them have reported positive results. However, to our knowledge there has been no study that meets all of these recommendations combining sleep, exercise, diet and sunlight exposure. Our study meets this challenge in a "real word" design: heterogeneous samples of depressed patients, with few exclusion criteria and in normal clinical practice conditions.

These measures, especially exercise and dietary, may be useful to prevent or improve many other medical conditions besides Depression. For example, comprehensive lifestyle changes including a low-fat vegetarian diet and moderate exercise may be able to induce regression of even severe coronary atherosclerosis [31]. Asking the patient to follow the clearly written recommended measures will require very little time on the part of the doctor. There will be almost no cost to the patient or the health system. Adverse effects resulting from these recommendations should be not expected.

### Main Strengths and Limitations

This is one of the first studies to evaluate the effectiveness of a lifestyle change intervention on depressive patients as carried out by regular staff members from several centers. Due to the fact that this intervention will be done in daily practice conditions, conclusions could be generalized without reservation. This strengthens considerably the external validity of the trial. The main limitation might be found in possible evaluation bias. Blind raters are informed about the hypotheses of the study. This might make them aware to which group the patients have been assigned. An involuntary bias of their rating cannot then be discarded. However, BDI self administered test could help us to disregard this possibility.

In conclusion, it is our intention to study the possible benefits of lifestyle changes for patients suffering from Depression by using a simple combination of hygienic-dietary recommendations on a written piece of paper. If successful, this would be a great support for doctors who might systematically recommend these simple measures to patients with such a serious disorder. We believe this finding could be particularly important for primary care, where Depressive Disorders are very common, especially among patients who are more frequent attenders [2,32].

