### Trial Procedures: Consent, Baseline Assessments, Blinding and Randomization

Collaborating researchers of the three participating institutions will identify all those potential patients who might meet the required criteria. During the recruitment visit patients will be informed of every detail of the study, answering all questions and concerns that they might have regarding their participation. Signed informed consents will then be collected (Table 1). Researchers will confirm that patients meet the criteria required for entry into the study using the Structured Interview MINI [23]. The following two questionnaires will later be administered: Beck Depression Inventory of 21 items (BDI-21) [24] and Questionnaire on Health Status (SF- 36) [25]. Finally, an appointment will be arranged within a week. During this baseline interview, a blind assessor will quantify the affective symptomatology through the Hamilton 17-item scale (HAMD-17) [26] and Clinical Global Impression scale (CGI). Subjects will then be checked to ensure that they do not show organic pathology which might induce symptoms of depression (EKG, BP, HR, BMI). The following tests will also be administered: blood count, biochemistry, coagulation studies, thyroid function tests, serology, levels of vitamins (folic acid and vitamin B12), and urine test with toxic levels, in addition to a pregnancy test if appropriate.

**Table 1 T1:** Study Schedule

	*WEEK 1/"TRIAGE"*	*WEEK O/BASELINE*	*WEEK 24*
Sociodemographic questionnaire		X	
			
Clinic questionnaire		X	X
			
MINI Interview	X		
			
Discussion of the study information leaflet	X		
			
Signed Consent Form	X		
			
Physical parameters			
• BP		X	X
• HR		X	X
• BMI		X	X
			
EKG		X	
			
Blood Test		X	X
			
Urine Test		X	X
			
Self Administered Test			
• BDI-21	X		X
• SF-36	X		X
			
Test administered by Blind Raters			
• HAMD-17		X	X
• GCI		X	X

Delivery of Hygienic-dietetic recommendations		X	

Patients will then be randomly assigned to one of two treatment arms according to sequence of entrance, using blocks of randomization. Patients assigned to the active treatment group will receive an envelope containing a sheet of paper with the four hygienic-dietary recommendations under consideration:

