### Outcome Measures

The primary variable of efficacy of the study will be the score of HAMD-17 obtained by the blind assessors before and after treatment. A full response is considered if the decline in scores on the HAMD-17 is greater than 50%, and a partial response if the reduction is between 25% and 50%. We will use BDI-21, filled out by the patient, and also the self-administered SF-36 and the GCI as secondary efficacy measures.

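### HAMD-17 raters know the study hypotheses, an avoidable risk of bias in the primary outcome, and the self-rated BDI is only a partial safeguard against it

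*Protocol article*

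**What the plan says.** Outcome Measures fixes the primary outcome and who scores it: "The primary variable of efficacy of the study will be the score of HAMD-17 obtained by the blind assessors before and after treatment". The BDI is a secondary measure: "We will use BDI-21, filled out by the patient, and also the self-administered SF-36 and the GCI as secondary efficacy measures". Table 1 lists the GCI (also written CGI) with the HAMD-17 under the blind raters, and the BDI-21 and SF-36 as self-administered.

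Main Strengths and Limitations then says of the raters: "Blind raters are informed about the hypotheses of the study". It continues: "This might make them aware to which group the patients have been assigned", and concludes: "An involuntary bias of their rating cannot then be discarded". The remedy offered is one sentence: "However, BDI self administered test could help us to disregard this possibility".

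On the patients' side, Trial Procedures says: "During the recruitment visit patients will be informed of every detail of the study". After the baseline assessment and randomization, "Patients assigned to the active treatment group will receive an envelope containing a sheet of paper with the four hygienic-dietary recommendations under consideration". Controls receive a matching envelope with non-specific advice on the same four topics.

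**The concern.** The primary outcome is a score given by an interviewer, so its credibility depends on the interviewer not knowing the arm. The article gives no reason why the raters need to know the hypotheses. A rater who knows what is being tested can make use of hints in the interview, and the active sheet supplies distinctive ones: a bedtime not before 11 at night, no naps, an hour's daily walk, two hours of sunlight, fish three times a week. The control sheet sets no such targets. The Background calls sleep disturbance a core symptom of depression, so sleep habits are a likely topic at the week-24 interview.

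The proposed check does not close the gap. The BDI is completed by patients who have read their sheet. If they expect to benefit, that expectation can lower their BDI and also colour their answers in the HAMD-17 interview. A reader of the results could then take agreement between the two scales as evidence against bias when it is not. The other efficacy measures do not fill the gap: the GCI comes from the same raters and the SF-36 from the same patients.

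**Working it through.** **1. Plan's own figure.** The article gives no figure for rater bias, so there is none to reproduce. Whether 34 per group follows from the stated assumptions is a separate question and does not affect this point. Here 34 is used only as the planned evaluable number, read as per group.

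**2. When bias can enter.** Trial Procedures places the baseline HAMD-17 and CGI before randomization, so there is no arm to detect at week 0. The exposure is at week 24.

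**3. What the BDI can and cannot show.**

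| HAMD-17 benefit | BDI benefit | Reading |
|---|---|---|
| Yes | No | Points to rater bias, since raters do not score the BDI |
| Yes | Yes | Fits a true effect, patient expectation moving both scales, or rater bias on the HAMD-17 together with patient expectation on the BDI |

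The second row is the one in which the article would want reassurance, and the BDI cannot separate its explanations.

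**4. Illustration of size.** Inputs from Power calculation: control mean 12 (SD 8), active mean 8 (SD 6), alpha 5% (taken as two-sided), 34 per group. The mean shift b in favour of the active arm is an assumption; no figure in the article supports any value.

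- Planned difference: 12 − 8 = 4 points.
- SE of the difference: √((8² + 6²)/34) = √(100/34) = 1.715.
- With no true effect, the chance of a significant result favouring the active arm is P(Z > 1.96 − b/SE), by normal approximation.

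| Assumed mean shift b | b/SE | 1.96 − b/SE | Chance of false benefit |
|---|---|---|---|
| 0 | 0 | 1.960 | 2.5% |
| 0.5 | 0.292 | 1.668 | 4.8% |
| 1 | 0.583 | 1.377 | 8.4% |
| 2 | 1.166 | 0.794 | 21.4% |
| 3 | 1.749 | 0.211 | 41.7% |

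If all 40 per group were evaluable, SE = √(100/40) = 1.581, and shifts of 1, 2 and 3 points give 9.2%, 24.4% and 47.5%.

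These are average shifts over the whole arm. If half the active patients were rated 2 points too low, the mean shift would be 1 point and the 8.4% row would apply.

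**The case against.** The strongest reply is that the article already names this as its main limitation and describes the mechanism, so much of the point repeats an admission. That is fair as regards the rater risk. What remains is that disclosure does not reduce an avoidable risk, and that the reassurance drawn from the BDI goes further than the BDI can support.

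Four stronger readings are tempting, and the article does not support them.

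- *Bias is built in.* The article says that knowing the hypotheses might reveal the arm. Knowing a hypothesis is not knowing an allocation, so a risk is documented and not a bias.
- *Patients are unblinded.* This is an inference. The statement about full information describes consent and does not say that patients learn which sheet is under test. The matching envelopes and topic-matched control advice look like partial masking. Balanced eating and sun precautions appear on both sheets, so mention of a topic alone need not identify the arm, although specific details could.
- *The BDI is worthless.* Raters do not score it, so it is informative against rater bias when the two scales disagree.
- *The plan treats agreement as confirmation.* The article says only that the BDI could help, and sets no decision rule.

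The objection that the 1, 2 and 3 point shifts are hypothetical also stands: a 3-point mean shift would be 75% of the planned effect. They are given here as a range of assumptions only.

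**Conclusion.** The point holds as a conceded, avoidable risk of rater bias in the primary outcome, with a safeguard that works in one direction only. It rests on three statements in the article: the raters know the hypotheses, they score the primary outcome, and the patient completes the BDI. It also rests on one modest inference, that patients who have read their advice may form expectations that affect both scales.

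The direction and size of any actual bias are unknown. If there were a mean shift of 1 point, a quarter of the planned 4-point effect, the chance of a false benefit would rise from 2.5% to about 8%; at 2 points it would be about 21% and at 3 points about 42%. These figures assume 34 evaluable patients per arm, the stated SDs, a two-sided 5% test and no true effect. The remedy is cheap, and ratings cannot be repaired once collected, so the change is worth making before the week-24 assessments.

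**What to change.** 1. Where feasible, have the week-24 HAMD-17 and CGI done by raters who have not been briefed on the hypotheses or on the content of either sheet. Unbriefed existing staff could, for example, rate patients from another of the three centres.
2. Before the week-24 rating, instruct patients not to mention the advice they received. This is not needed at week 0, because that rating precedes randomization.
3. After the week-24 rating, have the rater record a guess of the arm, and report the guesses descriptively by arm. Do not analyse HAMD-17 by correct versus incorrect guess: improved patients tend to be guessed active and unimproved ones control, so the strata are confounded with outcome and can create an appearance of bias.
4. Reword the BDI sentence in Main Strengths and Limitations to say that the BDI is patient-reported, is open to expectation, and cannot by itself rule out bias. It can add that a HAMD-17 benefit without a BDI benefit would suggest rater bias.

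Cost: a changed rater briefing, some scheduling across centres and one tick-box; no extra visits. Raters already briefed cannot be un-briefed. Where they have to be kept, only the patient instruction and the arm guess apply to their ratings, and the residual risk should be stated.

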## Abbreviations

CNS: (Central Nervous System); BP: (Blood Pressure); HR: (Heart Rate); BMI: (Body Max Index); ECG: (Electrocardiogram)
